**Figure 2 F2:**
[figure not shown]
Project timeline.

### Coaching for organizational change

The organizational coach for the first (pilot) site will be a member of the research team with extensive experience in organizational coaching. The next two sites will be coached by a physician from the pilot site, who will share firsthand experience in implementing Seva with subsequent clinics. Each site will have a designated ‘change leader’, a clinical leader at the site who is the point of contact with the coach and will coordinate implementation activities at the clinic; a ‘site coordinator’, a clinic employee who will enroll patients in the study and manage the day-to-day operation of Seva; and a ‘change team’, a group of four to eight clinical and/or administrative staff members who will help identify and make the organizational changes necessary to implement Seva. The coach will make an initial site visit during the four-month period of active implementation preparation to create a welcoming environment for Seva. During this visit, the coach will conduct a walk-through
[44] with change team members (an exercise in which employees experience the clinic as patients do, to reveal issues that need to be addressed); a work flow assessment using flow charting; and a technical assessment of data to be gathered and procedures needed to conduct the study. During this preparation period, the coach will also work with the change leader to ensure that pre-test data are collected; reviews of Seva are completed by clinical teams and their concerns addressed; and barriers to implementation rectified. After the initial site visit, for the remainder of the implementation preparation period and for the 12-month intervention period, the coach will have monthly telephone conferences with clinic staff and email correspondence as necessary to monitor implementation progress and offer advice and feedback to the staff. The coach and change leader will also work together to reduce organizational barriers to implementation.

### Study design

Our study uses a non-concurrent multiple-baseline design in which the start of the intervention period is staggered at the three sites by six months. The multiple-baseline design provides the intervention to all participants, but isolates the independent variable by introducing the intervention at specified points. Using the clinic as the unit of analysis, this single-subject approach will closely track the timing of intervention elements and repeatedly measure outcomes at the organizational level, including aggregated effects on clinicians, patients and practices. After pilot testing Seva at the first FQHC and improving Seva and the overall implementation strategy, we will introduce Seva at the second FQHC and then, six months later, at the third FQHC. Each FQHC acts as its own pretest control. During the 48-month data collection period, core organizational indicators will be measured via a staff survey (administered every 6 months) and the clinics’ electronic health records (aggregated across patients). While the non-concurrent multiple-baseline design may not provide as strong a basis for causal inference as a large RCT, we believe it is the appropriate design for evaluating the organizational impact of a system that has already been shown effective in RCTs of patients
[45]. We will also collect a set of standard CHESS/TES measures via a patient survey for comparison to previous studies that tested these technologies in RCTs, and to conduct exploratory analyses. The patient survey also provides supplemental clinical information not routinely collected in the clinics (*e.g*., addiction severity, quality of life, etc.).

### Evaluation framework

Our primary focus is to study how Seva is implemented in three FQHCs. In the process, we hope to generate insights on how Seva can be most helpful to organizations, staff and patients, thereby informing implementation processes in other FQHCs. Our evaluation includes patient, clinician, and organization-level outcomes. To organize this multifaceted evaluation, we use the RE-AIM framework
[46]. RE-AIM catalogs the quality, speed and impact of efforts to translate research into practice by including measures in five categories: reach, effectiveness, adoption, implementation and maintenance. The measures we will use are summarized in Table 
1, followed by a brief description of each dimension and selected outcomes.

**Table 1 T1:** RE-AIM measures

**Dimension**	**Measure**	**Source**	**Research question***	**Frequency**
Reach	Number of Seva patients (eligible, excluded, enrolled)	Patient survey	2	Pre
	Characteristics of participating patients	Patient survey	2	Pre
		EHR	2	Continuous
	Qualitative assessment- reach	Interview- clinic director	1	Pre
Effectiveness	No. patients screened for HIV	EHR	3	Continuous
	Healthcare utilization (hospitalizations, ER visits, and residential addiction treatment)	Patient survey	3	0 m, 6 m, 12 m, 18 m
		EHR	3	Continuous
	Treatment attendance	Patient survey	3	0 m, 6 m, 12 m, 18 m
		EHR	3	Continuous
	HIV risk behaviors	Patient survey	3	0 m, 6 m, 12 m, 18 m
	Substance use	Seva	3	Weekly
		Patient survey	3	0 m, 6 m, 12 m, 18m
	Quality of life	Patient survey	3	0 m, 6 m, 12 m, 18 m
	Qualitative assessment - effectiveness	Interview - clinic director	1	12 m
Adoption (setting)	Characteristics of participating clinics vs. general FQHC population	Publicly available uniform data system reports for FQHCs	2	Pre
	Readiness for implementation	Staff survey	2	Pre, every 6 m
Adoption (staff)	Use of Seva by staff (including characteristics)	Seva log files	2	Continuous
Adoption (patient)	Use of Seva by patients (including characteristics)	Seva log files	2	Continuous
Adoption (staff and patient)	Qualitative assessment- adoption	Staff interviews	1	Pre, every 6 m
		Patient interviews	1	12 m
Implementation	Stages of Implementation Completion	Staff interviews	1	Pre, every 6 m
	Technology acceptance	Staff survey	2	Pre, every 6 m
	Adaptations to protocol during intervention period	Staff interviews	1	Pre, every 6 m
	Cost of intervention	Staff interviews	1	Pre, every 6 m
		Coach logs	1	Continuous
	Qualitative assessment - implementation	Interview with clinic director, coach	1	12 m
Maintenance	Sustainability score	Staff survey	1	Pre, every 6 m
	Six-month follow-up on all effectiveness measures (see above) and use of Seva	Seva, Patient survey, EHR	1, 2, 3	Various
	Qualitative assessment - maintenance	Interview - clinic director	1, 2	18 m

*Source:* Re-aim.org; Measuring the Use of the RE-AIM Model Dimension Items Checklist

*(1) How can Seva be implemented in primary care settings efficiently and effectively? (2) To what extent do patients and staff accept and use Seva? (3) How does Seva affect clinical care for patients and staff?

#### Reach

In assessing reach, we will determine how many patients are eligible to use Seva within each clinic, how many are excluded, how many are invited to participate, and how many enroll in the study. We will also study how quickly patients are enrolled after the beginning of the enrollment period. We will assess how representative Seva enrollees are of the target population (substance using patients within each clinic) by comparing users to the target population on key clinical characteristics (*e.g*., treatment attendance, healthcare utilization). Qualitative assessment will supplement our data collection on reach. Our goal is to understand how clinicians perceive or anticipate which patients may benefit most from the system, because — for budget reasons — not all patients can have Seva, either in this study or in a broader dissemination. (In this study, we can offer Seva to a maximum of 100 patients per clinic.) For example, clinicians may select patients to enroll who they think will be strong models for other patients, or patients who have had many relapses and may benefit from a different treatment approach. As an implementation-focused study, we strive not for random selection but instead encourage clinicians to enroll patients for whom they believe Seva will be most helpful.

#### Effectiveness

Our primary effectiveness outcome is substance use. Other outcomes in the effectiveness domain will help us understand the impact of Seva on patients’ quality of life, HIV risk behaviors, healthcare utilization, and treatment attendance. We will also examine the extent to which the system promotes an overall increase in the proportion of substance-use patients screened for HIV. Healthcare utilization data (hospitalization, emergency room visits, and in-patient psychiatric treatment) will also be used in the cost analysis described below. Qualitative assessment of effectiveness will take place through an interview with the clinic director.

#### Adoption

In assessing adoption at the clinic level, we will report how many FQHCs were approached to participate and how many signed on to implement Seva. We will compare organizational characteristics of participating FQHCs to the more than 1,000 FQHCs in the United States, based on public reports required of these organizations by the federal government. We will gather qualitative data to assess which aspects of organizational structure affect implementation. To assess adoption at the staff level, clinic site coordinators will make a list of all staff members who see potential substance-using patients in primary or behavioral care, and invite these staff to complete surveys six months prior to the implementation period and every six months thereafter. The surveys include questions on job function (*i.e*., physician, behavioral health staff, or RN), which will allow us to assess how representative the respondents are of the clinic staff as a whole, and the Readiness for Implementation Survey
[47], an instrument used to predict the adoption success of information technologies in healthcare. Staff members and patients will take part in qualitative interviews to supplement data provided in the surveys to assess organizational barriers and facilitators related to implementation. We will analyze Seva log files to produce metrics about patterns of system adoption and use by patients and staff and assess the characteristics of individuals who use Seva most and least actively.

#### Implementation

To measure implementation progress, we will adapt our implementation model into a specific implementation plan (including timetables) for each clinic. We will employ the Stages of Implementation Completion model
[48] as a guide to assess the degree of implementation. Each phase of the implementation completion model is broken down into discrete tasks and events and presented as a checklist. We will assess whether each task/event was implemented, and the length of time each one took to implement. Starting at the beginning of the implementation-planning period (four months prior to implementation), the checklist will be reviewed and updated every six months by the site coordinator in conjunction with the implementation coach. Adaptations to the protocol will be noted. We will also assess implementation costs (see below) and administer the Technology Acceptance Model
[49], which helps explain factors that influence the use of a new technology. Qualitative assessment of the consistency of the intervention will occur through interviews with the clinic director and the implementation coach.

#### Maintenance

To assess maintenance, we will administer the British National Health Service’s Sustainability Index
[50]. The Sustainability Index assesses factors associated with sustainability potential, such as fit with organizational infrastructure, clinical leadership engagement, and progress monitoring. The Index also offers guidance, developed by an international panel of experts, on overcoming weaknesses. Factors measured by the Sustainability Index, along with those included in the Readiness for Implementation Survey, will guide us in building a conceptual model of barriers and facilitators to implementation. Assessing maintenance at the individual level includes monitoring of effectiveness measures (including substance use and quality of life) at the 18-month mark, 6 months after grant funding for phones and internet access ends. We will examine data on Seva use at the staff and patient levels to assess long-term maintenance of Seva. Qualitative interviews with clinic directors will assess the degree of institutionalization of Seva within organizations, how Seva aligns with clinical business models, and whether and how Seva was adapted after the active implementation period to promote maintenance.

### Analysis

We will use a mixed-method approach, using both quantitative and qualitative methods, to assess our implementation model. Our analysis follows guidelines for mixed-methods research promulgated by the NIH Office of Behavioral and Social Sciences Research
[51]. Because this is a study of the organizational impact of Seva, there will be no single-patient analyses; all analyses will be aggregated across patients.

Analysis of quantitative outcomes will proceed on three fronts:

1. Descriptive statistics will be used to assess relevant Reach outcomes.

2. Interrupted time series analysis will compare selected Effectiveness and Maintenance outcomes within a clinic before and after implementation. We will assess whether our implementation model promotes the successful installation and use of Seva using linear regression models, with each analysis having two time-series segments representing means and slopes before and after implementation. A test of the regression coefficient for implementation (a dichotomous variable indicating whether the time point occurred before or after implementation) will allow us to examine differences in the mean change at implementation. Differences in slope from pre- to post-implementation will be tested using the coefficient for the implementation x month interaction, where ‘month’ is a continuous variable indicating the month of measurement. Weighted least squares analysis will be used to account for potential differences in the number of patients or staff reporting outcomes within each clinic across time. Given the limited degrees of freedom, no covariates will be included in the models.

3. Drawing from conventional approaches to single-subject analysis, we will also compare selected RE-AIM outcomes within and across the clinics using data visualization
[52] to determine whether the shifts between intervention phases of the study generated shifts in the level, trend, and variability of performance
[53]. This will allow us to evaluate the immediacy, consistency and magnitude of the observed effects
[52].

The qualitative analysis is designed to:

1. Understand the environments in which Seva is implemented, how Seva was tailored to fit each environment, and the processes used to tailor Seva. Focus groups and observational and interview data will help us understand the environment and the processes used to tailor Seva.

2. Provide insights into the quantitative results. We will interview key stakeholders following each wave of surveys. As within- and across-site findings emerge, we will interview people who can help inform the findings.

3. Understand the barriers to and facilitators of implementing and sustaining Seva and how they relate to outcomes. Key stakeholders will be asked to reflect on reach, outcomes, adoption at the setting level, staff participation, implementation, and long-term effects.

4. Prompt informants to reflect upon how they might advise a similar FQHC to integrate Seva.

We will collect, transcribe and analyze field notes and interviews collected during each implementation phase using AtlasTi. The qualitative analysis will follow grounded theory to build a conceptual model of Seva’s implementation. Two researchers will independently analyze interviews that represent different organization-level stakeholders, and then meet to discuss and reconcile differences in interpretation. Because Readiness for Implementation Survey and Sustainability Index factors are associated with adoption and sustainability, we will include these factors as a priori themes, while seeking new insights generated from the interviews. Researchers will then code the remaining interviews, comparing themes to distinguish different types of organizations and conditions. To assure coding consistency, every fourth interview will be double-coded. Significant inconsistencies will be discussed and recoded. Finally, we will categorize the themes into a working model.

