### Timeline

Data will be collected from each FQHC for 48 months using a combination of data sources, including electronic health records, staff surveys/interviews, and patient surveys/interviews. We are collecting staff survey data every 6 months for 36 months, patient survey data every 6 months for 18 months, and aggregated EHR data for 48 months to cover the full time frame from the beginning of the pretest period at FQHC 1 to the end of the posttest period at the FQHC 3. Figure 
2 shows more information about the project timeline. Retrospective data collection will take place during the pretest period, using aggregated patient data from clinics’ electronic health records. During the pretest period, sites will also seek to identify potential patient candidates for recruitment. Full-scale implementation occurs during the subsequent 12 months, during which the sites receive coaching and actively recruit patients to use Seva. The sites will continue to be monitored during a post-test/sustainability period. During this period, sites may continue recruiting patients to use Seva, but without grant funding for phone/internet support or organizational coaching.

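### The two-segment before/after regression cannot show that the implementation model promotes use of Seva, and the staff-survey schedule is too thin to support it

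*Protocol article*

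**What the plan says.** Item 2 of the quantitative plan (Protocol article, Analysis) gives the scope: "Interrupted time series analysis will compare selected Effectiveness and Maintenance outcomes within a clinic before and after implementation". It then gives the purpose: "We will assess whether our implementation model promotes the successful installation and use of Seva using linear regression models". The form of these models is fixed in the same item, "with each analysis having two time-series segments representing means and slopes before and after implementation". Two coefficients are tested: the implementation indicator (change in level) and its product with month (change in slope). Staff-reported outcomes are within reach of the model: "Weighted least squares analysis will be used to account for potential differences in the number of patients or staff reporting outcomes".

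Table 1 (Evaluation framework) lists use of Seva under Adoption and again under Maintenance: "Six-month follow-up on all effectiveness measures (see above) and use of Seva". The Sustainability score is a staff-survey measure under Maintenance. Under Adoption, the site coordinators are to "invite these staff to complete surveys six months prior to the implementation period and every six months thereafter"; the Timeline gives "staff survey data every 6 months for 36 months". Study design says that each clinic is its own pretest control and that Seva is introduced at staggered dates. The study's purpose is stated under Evaluation framework: "Our primary focus is to study how Seva is implemented in three FQHCs".

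**The concern.** A before/after regression informs only if the before segment could have taken other values and is observed often enough to fit its line.

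- **Use of Seva.** No patient or clinician can use Seva before it is introduced, so the before segment is a structural zero. The null hypothesis for the level change becomes that Seva is not used at all. No clinic receives Seva without the implementation model, so even a clear rejection cannot be credited to that model.
- **Staff-survey outcomes.** The model has four parameters. One pre wave cannot give a pre-launch slope, and two fit it without error.

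At stake is what may be concluded on the study's main topic. A significant coefficient could be taken as support for the implementation strategy when it reflects only that the system went live.

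**Working it through.** The article states no power, alpha or sample-size figure, so there is none to reproduce. Assumptions added here: two-sided alpha 0.05, independent errors, equal weights.

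**1. Use of Seva: what the coefficients become.** With month *t* = 0 at launch, the model is

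E(Y) = b0 + b1·t + b2·I + b3·I·t, with I = 1 after launch.

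All pre-launch values are 0, so b0 = b1 = 0 exactly. Hence b2 is the fitted use at launch and b3 is the post-launch slope.

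**2. Use of Seva: how easily the level test rejects.** Take 100 enrolled patients (the cap given under Reach), 5 active in an average month, no trend, 12 pre-months and 18 post-months.

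- Monthly SD of the share: σ = √(0.05 × 0.95 / 100) = 0.0218, so the level is 0.05 / 0.0218 = 2.29σ.
- Variance factor of b2: pre 1/12 + 6.5²/143 = 0.379; post 1/18 + 8.5²/484.5 = 0.205; sum 0.584, square root 0.764.
- The residual SD is diluted by the exact zeros: √(16/26)·σ = 0.784σ.
- Typical t = 2.29 / (0.764 × 0.784) ≈ 3.8, against a critical value of 2.06 on 26 df.

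Simulation of the same set-up (binomial use, 10,000 series per cell), percentage of series with a significant level change at 5 of 100 active:

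| Pre-months | 12 post | 18 post | 24 post |
|---|---|---|---|
| 6 | 73 | 77 | 82 |
| 12 | 98 | 99 | 99 |
| 18 or 24 | >99 | >99 | >99 |

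A Poisson version with 18 post-months gives 74%, 99% and 99.9% for 6, 12 and 18 pre-months. Runs with other seeds and lengths gave figures down to 72% for 6 pre-months and 97% for 12 or more. At 20 of 100, rejection is essentially 100% throughout, so the test does not distinguish 5 users from 20. Rejection is not universal: at 2 of 100 with 6 pre-months it is only about 15–23%.

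In the Poisson runs the interaction equalled the post-launch slope every time. With flat use at 5 of 100 it rejected in 0%, 0.4% and 5.7% of series (6, 12 and 18 pre-months), against a nominal 5%. Its standard error is therefore also distorted by the zero segment.

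**3. Staff survey: what the schedule supports.** First wave at month −6, then every 6 months over 36 months: −6, 0, 6, 12, 18, 24, 30 (7 waves).

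- *Month 0 counted as post:* one pre wave. The design matrix has rank 3 for 4 parameters. The slope change is not estimable, and the level change needs an assumed pre-launch slope.
- *Month 0 counted as pre:* two pre waves. Rank 4, pre-segment fitted exactly, 7 − 4 = 3 residual df, critical t 3.18. The variance factor of the level change is 1 (pre line at month 0) + 1/5 + 18²/360 = 2.1, so SE = 1.45 SD, where SD is the residual SD of a clinic's wave mean. Power for a shift of 1, 2 or 3 SD is 8%, 17% or 31%; 80% power needs about 6.2 SD. With 6 waves, 2 df remain and 80% power needs about 8.9 SD.

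**4. Contrast.** A monthly health-record series of 36 points has 32 df. It needs about 2.1 SD of the monthly mean (12 pre-months) or 2.9 SD (6 pre-months) for 80% power, and its pre-launch values are real observations.

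**The case against.** The strongest reply is that the quoted sentence states an aim and does not name log-file use as a dependent variable. Item 2 is limited to selected Effectiveness and Maintenance outcomes; Table 1 places use mainly under Adoption; the Adoption text describes log-file metrics with no before/after contrast; and the Abstract's example of the time-series analysis is treatment attendance. This leaves real room about which outcomes enter. It does not remove the problem: the sentence ties these regressions to use, and use reappears in a Maintenance row, a class named for the analysis.

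A second reply is that the plan specifies weighted least squares. If the outcome is the share of enrolled patients and the weight is the number enrolled, pre-launch months have zero weight. That is fair against the exact percentages, as is the assumption of 100 enrolled from the first month. But the before segment then vanishes and the before/after contrast cannot be estimated, so the test is not rescued.

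On staff outcomes, only the Sustainability score clearly falls in a named class, and it is not committed. The article itself concedes limited degrees of freedom. Study design places the survey in a 48-month period and Figure 2 is not shown, so later sites might have more pre waves. With three pre waves 80% power still needs about 6.5 SD, and with four at the third site about 4.7 SD.

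Stronger readings that a reader might infer are not supported:

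- *That this is the only evidence on implementation.* The stages-of-completion checklist, enrolment counts, log-file metrics, visual analysis and interviews all bear on it.
- *That a clinic where Seva failed would be declared a success.* Nothing makes a significant coefficient the success criterion, and low use would show elsewhere.
- *That all these tests are worthless.* The interaction for use still indicates post-launch growth or decay, and the staff model can be computed with two pre waves.

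**Conclusion.** The concern holds in a limited form. If use of Seva enters the two-segment model, its level test is close to a foregone conclusion even at poor uptake, and its slope test describes only the post-launch trend; neither bears on whether the implementation model caused the use. The rejection rates (about 72–82% with 6 pre-months, at least 97% with 12 to 24, at 5 of 100 active) rest on unweighted least squares, alpha 0.05, 100 enrolled and flat use. The structural argument needs none of these.

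For staff-survey outcomes entered in the model, the Adoption schedule leaves the slope change either not estimable or, with 7 waves, on 3 residual df with very low power. Monthly health-record outcomes share neither defect. The plan should be changed, because the correction is cheap and alters what can be concluded.

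**What to change.** 1. Keep the two-segment model for monthly health-record outcomes.
2. For Seva use, drop the pre-segment. Report the post-launch monthly share of enrolled patients, and of listed staff, who are active, with a break when grant support ends. Judge it against a target the team fixes before launch, and make no before/after significance claim. The article gives no use rates from the earlier TES or A-CHESS trials, so the team must justify the target itself.
3. For staff-survey outcomes, drop the slope-change term and compare the pre wave or waves with later waves within each clinic, with intervals. State whether the month-0 wave is pre or post. These intervals will still be wide: with 7 waves, the 95% half-width is 2.57 × √(1/2 + 1/5) ≈ 2.2 SD for two pre waves and 2.57 × √(1 + 1/6) ≈ 2.8 SD for one.
4. Reword the purpose sentence so that it no longer ties the before/after regression to use.

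The cost is analysis wording only; the log files and staff surveys are already planned. The team commits to a use target that it could miss, and gives up a staff slope test that the schedule cannot support.

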**Methods/Design:**

Our implementation strategy uses three models of organizational change: the Program Planning Model to promote acceptance and sustainability, the NIATx quality improvement model to create a welcoming environment for change, and Rogers’s diffusion of innovations research, which facilitates adaptations of innovations to maximize their adoption potential. We will implement Seva and conduct an intensive, mixed-methods assessment at three diverse Federally Qualified Healthcare Centers in the United States. Our non-concurrent multiple-baseline design includes three periods — pretest (ending in four months of implementation preparation), active Seva implementation, and maintenance — with implementation staggered at six-month intervals across sites. The first site will serve as a pilot clinic. We will track the timing of intervention elements and assess study outcomes within each dimension of the Reach, Effectiveness, Adoption, Implementation, and Maintenance framework, including effects on clinicians, patients, and practices. Our mixed-methods approach will include quantitative (*e.g*., interrupted time-series analysis of treatment attendance, with clinics as the unit of analysis) and qualitative (*e.g*., staff interviews regarding adaptations to implementation protocol) methods, and assessment of implementation costs.

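### The interrupted time-series regression has one break and no term for the end of the 12-month supported period, so it cannot separate maintenance from active implementation

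*Protocol article*

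**What the plan says.** The abstract (Methods/Design) states that the design "includes three periods — pretest (ending in four months of implementation preparation), active Seva implementation, and maintenance". The Timeline section gives the active period 12 months, with coaching and active recruitment. Sites are then monitored in a period when they may go on recruiting patients to Seva, "but without grant funding for phone/internet support or organizational coaching". The end of the active period is therefore a planned change at a known date.

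Quantitative item 2 of the Analysis section states: "Interrupted time series analysis will compare selected Effectiveness and Maintenance outcomes within a clinic before and after implementation". It fixes the model as linear regression, "with each analysis having two time-series segments representing means and slopes before and after implementation". The phase variable is "a dichotomous variable indicating whether the time point occurred before or after implementation". On trend, "Differences in slope from pre- to post-implementation will be tested using the coefficient for the implementation x month interaction". No other phase term is given, and covariates are ruled out because degrees of freedom are limited.

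Other assessments of maintenance are listed in the Maintenance section, in Table 1 and in item 3 of the Analysis section: effectiveness measures at 18 months, Seva use, the Sustainability Index, clinic director interviews, and visual comparison of level, trend and variability across phases.

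**The concern.** The design has two planned interruptions and the regression has one. If every month from go-live onward is coded as after implementation, months with coaching and funded phones are fitted on the same straight line as months without them. The model then has no parameter for the change at withdrawal and none for the level in the maintenance period, although Maintenance outcomes are assigned to it.

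This is more than detail left to a fuller document. The article itself fixes the number of segments, the indicator and the interaction, and that model does not match the article's own three-period design.

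Maintenance is one of the five RE-AIM dimensions, and early attention to sustainability is named as a distinguishing feature of the implementation model. An effect that holds while support lasts and then drops is a different finding from one that erodes from the first month. The two-segment model cannot tell them apart.

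**Working it through.** The article gives no power, alpha or effect size for this analysis, so there is no figure to reproduce. The check asks what the stated model returns when an effect changes at the end of support.

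**Inputs from the protocol.** 48 months of aggregated EHR data (Timeline), treated as 48 monthly points per clinic; 12 active months; a four-parameter model (intercept, month, indicator, interaction).

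**Assumptions.** Figure 2 is not shown, so go-live is placed after month 6, 12, 18 or 24. The pretest series is flat. The true effect is +10 in the 12 supported months and then falls by L. Month is counted from go-live. There is no noise, and for standard errors the errors are independent with SD σ.

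**Two-segment fit.** The pretest line is fitted exactly at zero, so the post-go-live line is an ordinary regression on n = 12 + m months, where m is the number of maintenance months:

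- slope change = -6 × L × 12 × m / [n(n² - 1)]
- step = mean of the n months - slope × (n - 1)/2

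For go-live after month 6, m = 30, n = 42 and L = 10. The slope is -6 × 10 × 12 × 30 / (42 × 1763) = -21600/74046 = -0.29. The mean is 120/42 = 2.86, so the step is 2.86 + 0.2917 × 20.5 = 8.8.

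| Go-live after month | m | Step (truth 10) | Slope change (truth 0) | Fitted, 12th supported month (truth 10) | Fitted, final month (truth 0) |
|---|---|---|---|---|---|
| 6 | 30 | 8.8 | -0.29 | 5.6 | -3.1 |
| 12 | 24 | 9.8 | -0.37 | 5.7 | -3.2 |
| 18 | 18 | 11.0 | -0.48 | 5.7 | -3.0 |
| 24 | 12 | 12.2 | -0.63 | 5.3 | -2.2 |

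**Smaller losses.** The slope is proportional to L. With half lost it is -0.15 to -0.31; with a quarter lost, -0.07 to -0.16; with none lost, 0.

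**Three-segment fit.** Adding an indicator for the maintenance period and its interaction with months since withdrawal recovers a step of +10, a slope change of 0 and a withdrawal change of -10 exactly. Residual df go from 48 - 4 = 44 to 48 - 6 = 42.

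**Precision (in units of σ).**

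| Go-live after month | Step SE, 2 to 3 segments | Ratio | Slope-change SE, 2 to 3 segments | Ratio |
|---|---|---|---|---|
| 6 | 0.98 to 1.08 | 1.10 | 0.239 to 0.253 | 1.06 |
| 12 | 0.70 to 0.82 | 1.18 | 0.085 to 0.118 | 1.39 |
| 18 | 0.61 to 0.73 | 1.21 | 0.050 to 0.095 | 1.90 |
| 24 | 0.58 to 0.69 | 1.19 | 0.042 to 0.089 | 2.13 |

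**Survey outcomes.** Staff surveys every 6 months for 36 months give 7 waves if both ends count. If they run from month -6 to 30 and the wave at go-live counts as after, only one wave precedes implementation, and even the two-segment model is not identified (rank 3 of 4). The four patient-survey waves give rank 2 or 3 of 4, depending on how month 0 is coded.

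**The case against.** **Maintenance is assessed elsewhere.** A reader might infer that maintenance is never assessed. The document does not support that, given the other measures it lists. The narrower gap stands: visual comparison gives no estimate with a stated uncertainty, the Sustainability Index measures potential for sustainability rather than outcome levels, and no regression coefficient refers to the end of support.

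**Pooling is inferred.** The text does not say outright which months count as after, and each analysis having two segments could describe separate pretest-versus-active and pretest-versus-maintenance fits. That reading is possible, but nothing states it, and the single before/after indicator points the other way. If it is what was meant, one sentence settles the matter.

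**The example is a worst case.** Total, immediate loss is assumed, while Seva itself is not withdrawn. This stands, and the smaller-loss figures show how the distortion shrinks. With a quarter lost, the fitted mean over the maintenance months is 7.8 against a truth of 7.5.

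**Conclusions for dissemination.** A reader might infer that the two-segment model leads to the opposite advice. It does not. Under full loss it still shows a clear early gain that is not sustained, and the phase plots should reveal an abrupt drop. What it gets wrong is when and how the loss occurs.

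**Precision and scope.** A third segment is a trade of bias against variance, and the slope-change test can lose half its precision. It suits only monthly EHR series. Patient-reported substance use, from the survey behind the primary effectiveness outcome, has too few waves, and the healthcare utilization analyses are declared exploratory. These limits stand and narrow the fix. For a 48-month EHR series, however, the cited shortage of degrees of freedom does not rule it out.

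**Conclusion.** The point holds in limited form. As specified, the regression has no term for the end of active support, so for the Maintenance outcomes assigned to it, it cannot distinguish the maintenance period from active implementation. No other listed method is specified as a model-based estimate of the change when support ends.

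The size depends on how much effect is lost. For a 10-unit effect fully lost at withdrawal, the spurious slope change is -0.29 to -0.63 per month, and the fitted effect in the last supported month is about 5.3 to 5.7 instead of 10. These figures rest on assumed go-live months, an abrupt loss and a flat pretest series. With no loss there is no distortion, but whether there is loss is what the maintenance analysis is meant to find out.

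This should be fixed. It does not undermine the study: its main focus is how implementation proceeds, and maintenance is covered by several other measures.

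**What to change.** For the monthly EHR outcomes only, add a second break at the end of the active period. With t0 for go-live, t1 for the end of support, I = 1 from t0 and M = 1 from t1:

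Y = b0 + b1(t - t0) + b2·I + b3·I(t - t0) + b4·M + b5·M(t - t1)

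Report three contrasts with intervals:

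- effect at the end of active support: b2 + b3(t1 - t0)
- change at withdrawal: b4
- maintenance level against the projected pretest trend at a named month t: b2 + b3(t - t0) + b4 + b5(t - t1)

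Keep the six-monthly staff and patient survey outcomes descriptive, because they have too few waves. If separate pretest-versus-active and pretest-versus-maintenance fits were intended instead, say so and state which months enter each.

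The cost is two parameters per series (44 to 42 residual df at 48 points) and no new data. The step SE rises by about 10-20%. The slope-change SE rises by about 6% with go-live after month 6 and roughly doubles with go-live after month 18 or 24.
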